### 2.8. Selection Criteria

See Table 2 for detailed information.

## 3. Results

### 3.1. Descriptive Data

The following data will be collected: age, sex, BMI, duration of pain in months, previous treatments, current symptoms in other joints, comorbidities, use of medications, treatment expectations, educational level, individual and per capita income, level of education attained by the main breadwinner and occupational category of the main breadwinner.

### 3.2. Primary Outcome

The intensity of the pain will be evaluated through the VAS [37]. The average of the last seven days (VAS-7D) will be asked to rate their pain by marking on a continuous line of 100 millimetres (0 = “no pain” and 100 = “worst imaginable pain”).

### 3.3. Secondary Outcomes

Moreover, the intensity of the pain at rest (VAS-R) and walking on flat ground (VAS-W) will be evaluated. Functional capacity will be assessed through the Western Ontario and McMaster Universities Osteoarthritis Index (WOMAC). In addition, physical performance will be measured (gait speed test [38], 30-s chair stand test, timed up and go test and unipodal stance task), pain-related interference (VAS [39]), pain-related distress (VAS [39]), pressure pain threshold and quality of life in older adults (WHOQOL-BREF), global change (Patient-perceived satisfactory improvement; PPSI), global patient assessment (5 points Likert scale), and session attendance (physical therapist treatment notes). Finally, adverse events will be recorded (i.e., perception of any problem that the participants attribute to their participation in the study, which causes absence from two or more sessions).

### 3.4. Other Measurements

A variety of other measures will be collected further to analyse possible moderators and mediators of clinical effects. These measures will not be used to determine treatment efficacy. These measures include kinesiophobia (Kinesiophobia TAMPA Scale), sleep quality (Pittsburgh Sleep Quality Index), pain catastrophism (Pain Catastrophism Scale [40]), negative affectivity (DASS-21), expectation for overall improvement (5-point Likert scales), and self-efficacy (Chronic Pain Self-Efficacy Scale). Finally, the medication during treatment sessions should be reported.

### 3.5. Procedures

#### 3.5.1. Evaluations

Two physiotherapists blinded to the intervention (i.e., other than the treating physiotherapists) will perform the initial assessments, assessments at the end of the intervention and assessments at 1 and 3 months of follow-up. The research team will train them in a 4 h training for the application of the evaluation. The evaluations will be carried out in the Physiotherapy Laboratory at the Universidad de La Frontera. The results of the evaluators’ measurements will be recorded on a paper registration form specially designed for the study. This registration form will have a numerical code for each participant to avoid their identification. For the self-report questionnaires, the evaluators will check the data submitted by the participants to verify the correct and complete data entry.

For the evaluation, only the affected knee will be focused on. For participants with bilateral symptoms, the single knee will be the one with the most symptoms. In the case of presenting similar symptoms in both knees, the right one will be considered dominant.

#### 3.5.2. Interventions

Two physiotherapists will provide the intervention. They will be trained in a 6 h training before the start of the study. ’They will also be given written material with the intervention’s details (exercises, progression, etc.). The researchers will provide the necessary documents for the execution of the study. New physiotherapists will follow the same training and monitoring procedure if required. Participants will continue with the treatment indicated by the treating physiotherapist, being registered by the study staff.

On the other hand, they will be instructed to avoid therapies complementary to the one indicated by the doctor (i.e., balneotherapy, reiki, chiropractic) and inform the treating physiotherapist if they do so.

*Transcutaneous Vagal Stimulation*: TVS will be applied, in line with other research [15,16,18,41], through a portable TensMed S82 electrostimulation device (Enraf Nonius). The auricular electrode clips (Auricular Clips, Body Clock Health Care Ltd., London, UK) will be placed for active condition in the left ear (see Figure 2)., specifically in the auricular cymba concha, given that stimulation of the left vagus nerve has not been shown to cause abnormal activity in the heart [42]. That stimulation of the right vagus nerve could affect the heart’s activity as it has direct efferent fibres with projection to this organ [43]. The device will be programmed with a biphasic square current at an intensity that produces a clear tingling sensation that is neither uncomfortable nor painful [41], with pulses of 300 microseconds, at 25 Hertz, the stimulus will be present for 30 s and will be followed by a 30-s rest period [15,18]. TVS will be placed and programmed before each exercise session being used during the whole session. In this vein, it is important to note that a systematic review showed that TVS has been shown to be safe and tolerable in multiple populations [44] with minimal side effects such as slight itching and redness of the skin [42]. The device will be configured with the same parameters and intensity described above for sham TVS condition. However, the device will be located in the left earlobe [45] (see Figure 2). This area does not have vagal innervation, and more importantly, it has been proven that it does not produce any activation in the cortex or brain stem [46].

*Exercise program*: Both groups will carry out a tailoring exercise program in 12 sessions, of approximately one hour, distributed in 3 sessions per week for a month. The exercise program will be administered in person, keeping a ratio of 1 physiotherapist per 3 participants at the most. The objectives of the program will be to reduce pain and improve functional capacity. The program includes a warm-up stage (i.e., stationary bicycle), a central stage of strengthening and stretching exercises of the knee, hip and lumbar zone muscles, and finally, a stage of returning to calm [47]. Each exercise will have 5 levels of difficulty (from 1 = easy to 5 = difficult). All participants will start at level 3, increasing or decreasing in level depending on the pain they experience and their ability to perform the exercises. In addition, the physiotherapist in charge of administering the programme will assess session by session whether the difficulty of the various exercises should be adjusted. (i.e., tailoring). This program was designed based on the findings of literature reviews and meta-analyses (Appendix A) [12,48,49,50].

Both groups will carry out the same exercise program. The physiotherapists will record the attendance to the treatment sessions and each patient’s progress in a record book.

If a patient does not attend on the stipulated date, he/she will be contacted by phone on the same day to find out the reason for the absence, and he/she will be gently invited to attend the next day to comply with the scheduled session. If a patient does not attend two consecutive sessions, the principal investigator will contact him/her to consult the reason for non-attendance and invite him/her to continue with the study. Regular face-to-face meetings will be held between one of the investigators and the treating physiotherapists to reinforce the intervention protocols and discuss study issues, which will help ensure the uniform application of the treatment.

In every session, the physiotherapists will make a brief evaluation to determine the progress of the exercise program. Additionally, the session could be rescheduled if pain or inflammation is preventing the correct performance of the session. In this case, the idea is to maintain 3 sessions per week at least. Adverse events that the patient attributes to the use of TVS or the exercise program will be analysed jointly by the treating physiotherapists and the patient to assess the possible discontinuation of the intervention.

### 3.6. Data Analysis

All statistical analyses will be performed using the statistical software program STATA v16. A descriptive analysis of the main variables of the study will be carried out using central tendency statistics (mean, median, mode, etc.) and dispersion statistics (standard deviation, variance, range, etc.). The baseline variables will be reviewed to evaluate the comparability of the groups. The primary outcome measure was the average pain VAS measured at 4 weeks after randomization. TVS was compared with TVS sham using an analysis of covariance (ANCOVA) model that included a TVS sham group as the factor of interest and the corresponding baseline average pain VAS as a covariate. The primary analyses included all available data from all randomized participants. Missing data were accommodated using the technique of multiple imputations. Statistical analyses will be performed according to the intention to treat principle. An alpha level of 0.05 will be accepted as significant. Results will be reported as a minimum between-group mean squared differences and 95% confidence intervals from baseline to end of follow-up.

A secondary analysis compared the percentage of “responders” between groups [51] using a chi-square test. A “responder” was defined as a participant whose VAS pain scores at 4 weeks improvement by at least 20% relative or 15 mm absolute from baseline or was below 40 of 100 [52]. Participants who prematurely discontinued were defined as non responders. Prespecified analyses of secondary outcome variables used similar ANCOVA models to those of the primary analyses. No adjustment for multiplicity was made in the secondary analyses, as they were considered exploratory and hypothesis generating.

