**EVALUATIONS**						
Descriptive data		**X**				
Primary variable		**X**		**X**	**X**	**X**
Secondary variables		**X**		**X**	**X**	**X**
Other variables		**X**				

**Table 2 ijerph-20-00311-t002:** Eligibility criteria.

Inclusion Criteria	Exclusion Criteria
Women and men aged 55 and over The medical diagnosis of knee osteoarthritis according to the clinical criteria of the American College of Rheumatologists Chronic pain (i.e., 3 months or more) Average pain of the last seven days among 30 mm and 80 mm on the Visual Analogue Scale Walking without technical aids or knee brace Availability to attend an exercise program three times a week for four weeks Access to communication via telephone Agreement to participate in the study by signing an informed consent form	Presence of the following symptoms and signs: Fever or chills, large effusions, paresthesias or paresis of the lower limb Presence of medically diagnosed psychiatric or neurological diseases (cognitive impairment, Alzheimer’s, Parkinson’s, epilepsy, moderate or severe depression, bipolar disorders, obsessive compulsive disorder, etc.) Neuromuscular or cardiac disorders (i.e., arrhythmia, conduction cardiac block), stroke, generalised rheumatology, diabetes mellitus II, morbid obesity (i.e., equal to or greater than III) Medical contraindication of physical exercise Joint infiltration or lower limb surgery in the previous 6 months Surgery is planned for the next 6 months Take strong regular two or more kinds of medication Conditions that affect the lower limb and/or limit its functional capacity, such as previous fractures in the area, deformity, joint replacement, tibial osteotomy Participation in exercise programs in the last nine months Inability to follow instructions

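### The blanket ANCOVA rule for secondary outcomes cannot be followed as written for perceived improvement, attendance and adverse events, which have no baseline value; baseline adjustment of the responder analysis is an optional gain

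*Protocol article*

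**What the plan says.** Section 3.6 (Data Analysis) of the protocol article fits the primary outcome with an ANCOVA containing treatment group and "the corresponding baseline average pain VAS as a covariate". It then sets one rule for the rest: "Prespecified analyses of secondary outcome variables used similar ANCOVA models to those of the primary analyses". No exception is made by type of outcome.

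Section 3.3 (Secondary Outcomes) mixes scales. Besides continuous measures it lists "global change (Patient-perceived satisfactory improvement; PPSI), global patient assessment (5 points Likert scale), and session attendance", and it adds that "adverse events will be recorded (i.e., perception of any problem that the participants attribute to their participation in the study", counting only problems that lead to two or more missed sessions. Table 1 has one row, "Secondary variables", marked at baseline, end of intervention, month 2 and month 4.

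The responder analysis has its own sentence in section 3.6: "A secondary analysis compared the percentage of “responders” between groups [51] using a chi-square test". A responder has a VAS fall of 20% or of 15 mm, or a week-4 score under 40 mm. Table 2 admits baseline scores from 30 to 80 mm. Section 3.6 labels the secondary analyses exploratory and makes no multiplicity adjustment.

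**The concern.** A model built like the primary one needs the outcome's own baseline as covariate. Some of the listed outcomes come into being only once treatment has started, so the stated rule has nothing to enter for them. The article does name a model for these outcomes, so this is not a detail left to a fuller document. The named model does not fit three of them. If the text stays as it is, the analyst must choose both covariate and model for these outcomes later, although the analyses are called prespecified.

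A second, lesser matter is the responder comparison. Response depends on baseline VAS, which is collected from everyone and already used in the primary model, yet the chi-square leaves it out. At stake there is some precision, not validity.

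**Working it through.** **Which outcomes can have a baseline value.** This is a reading of sections 3.3 and 3.6 and Table 1; no arithmetic is needed.

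| Outcome | Pre-treatment value possible? | Rule in 3.6 usable as written? |
|---|---|---|
| Continuous measures (VAS-R, VAS-W, WOMAC, performance tests, pressure pain threshold, WHOQOL-BREF) | Yes | Yes |
| 5-point global patient assessment | Yes, if taken at baseline | Yes, then |
| PPSI | No: it rates change since the start | No |
| Session attendance (0 to 12) | No: sessions follow assignment | No |
| Adverse events | No: attributed to participation and tied to missed sessions | No |

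For the last three rows the baseline mark in Table 1 cannot hold either.

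**Does a linear model fail on the non-continuous outcomes?** Type I error of a linear two-group comparison, 35 per arm, 20,000 simulated trials:
- 5-point score with assumed category probabilities 0.10, 0.20, 0.30, 0.25, 0.15: 0.0495.
- Yes/no adverse event at an assumed rate of 5%: 0.038; at 10%: 0.060.

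The error rate stays near nominal. What remains is the missing covariate, and that a mean difference is an awkward summary for a yes/no event or a count capped at 12.

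**Responder analysis.** The plan gives no figure for it, so there is nothing to reproduce.

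Inputs from the article: 35 per arm and change SD 21.5 mm (section 2.7); entry range 30 to 80 mm (Table 2); responder rule (section 3.6). Assumptions: baseline *b* uniform on 30 to 80; control improvement 8.6 mm; change independent of baseline; change SD also tried at 10 mm; no dropout. Then *y* = *b* − 8.6 − δ × arm + N(0, SD²), limited to 0 to 100, and response if (*b* − *y*)/*b* ≥ 0.20, or *b* − *y* ≥ 15, or *y* < 40.

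Dependence on baseline at SD 21.5 with δ = 0: 73% respond at baseline 30–39.9, 53% at 40–54.9 and 41% at 55–80. A participant who enters below 40 and does not change at all is already a responder. Under the uniform baseline that is (40 − 30)/(80 − 30) = 20% of participants.

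Rejection rates over 3,000 trials per row, chi-square without continuity correction against the likelihood-ratio test from logistic regression on arm and baseline:

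| SD (mm) | δ (mm) | Chi-square | Adjusted logistic |
|---|---|---|---|
| 21.5 | 0 | 0.051 | 0.054 |
| 21.5 | 8.6 | 0.219 | 0.256 |
| 21.5 | 17.2 | 0.677 | 0.703 |
| 10 | 0 | 0.043 | 0.055 |
| 10 | 8.6 | 0.656 | 0.727 |
| 10 | 17.2 | 0.991 | 0.982 |

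With a different assumed baseline (normal 55/15 truncated to 30–80), a control improvement of 15 mm and SD 21.5, 4,000 trials per scenario gave 4.7% against 4.8% (δ = 0), 24.2% against 25.4% (δ = 8.6) and 63.9% against 67.5% (δ = 17.2).

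Across both baseline shapes and SDs from 10 to 21.5 mm the gain is roughly 1 to 8 points where power is not near 100%, and about 1 to 4 points at SD 21.5. The likelihood-ratio test can run about a point higher in type I error (0.055 against 0.043 at SD 10), so part of the apparent gain comes from that.

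**How much chance baseline imbalance matters.** In the truncated-normal simulation the SD of the difference in mean baseline is 2.8 mm, and each mm moves the risk difference by about 0.7 points: 2.8 × 0.7 ≈ 2 points. The standard error of the risk difference is √(2*p*(1 − *p*)/35), which is 12.0 points at *p* = 0.5 and 11.0 at *p* = 0.7. The imbalance share of the variance is (2/12.0)² to (2/11.0)², or about 3%.

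**The case against.** The strongest reply is that the rule asks for similar models, not identical ones. An analyst could put baseline VAS-7D in as covariate for every outcome, and that model would run. This stands as far as it goes: a reader who concludes that no ANCOVA could be fitted to these outcomes goes further than the text allows. But section 3.6 does not say that this is meant, the only pattern it gives is the outcome's own baseline, and Table 1 implies that such a value exists for all of them.

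A reader might also infer that linear models would give bad standard errors here, or that the 5-point assessment needs a proportional-odds model. The checks support neither. That assessment can be taken at baseline, and its simulated error rate is nominal.

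A reader might further infer that the responder chi-square is wrong because chance baseline imbalance feeds into it. It is a valid test under 1:1 randomisation. Such imbalance is ordinary sampling variation that the test already allows for, and about 3% of the variance here. The dependence on baseline comes from the responder definition, chiefly the under-40 criterion combined with entry from 30 mm. Adjustment would not stop an unchanged participant from counting as a responder.

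Finally, these analyses are declared exploratory. That limits the impact, but a prespecified model should still be one that can be followed.

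**Conclusion.** The point holds for three outcomes. PPSI, session attendance and adverse events have no pre-treatment value, so the stated ANCOVA rule cannot be followed as written for them, and the Table 1 row is wrong in marking them at baseline. This rests on the article's own wording and needs no numerical assumption.

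The responder chi-square is not an error. Adjusting it for baseline VAS-7D is a cheap improvement of roughly 1 to 8 points of power, towards the lower end (about 1 to 4) at the SD the plan states. Those figures depend on the assumed baseline distribution, the control improvement and change being independent of baseline, none of which the article gives.

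Severity is minor: the primary analysis, its sample size and the trial's main conclusion are untouched.

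**What to change.** In section 3.6, replace the single sentence by a rule for each outcome type:
- Keep ANCOVA with the outcome's own baseline for secondary outcomes measured at baseline. The 5-point global assessment may stay in this group if it is taken then.
- Analyse PPSI with a logistic or ordinal model, according to how it is scored, adjusted for baseline VAS-7D.
- Report session attendance and adverse events by arm, with a between-arm difference and 95% CI.

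In Table 1, split the secondary-variables row so that these three outcomes carry no baseline mark.

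Optionally, replace the responder chi-square by logistic regression on arm and baseline VAS-7D, and report the standardised risk difference with 95% CI. The under-40 element of the responder definition is a separate matter that this change does not settle.

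The cost is a few sentences, one table edit and slightly more programming. No new data are needed. The adjusted responder test may run about a point above the chi-square in type I error at this sample size.

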## 4. Discussion

KOA clinically presents with various symptoms, including pain, stiffness, instability, and significant limitations in daily activities [53]. This results in an explicit restriction in social participation and a subsequent decrease in quality of life. In this scenario, KOA treatment strategies range from pharmacological and physiotherapy treatments to surgical interventions [34]. However, in terms of their efficacy, they still show limitations.

In this context, it is essential to find new treatments for KOA. TVS has been proven as a suitable technique to inhibit pain [16,21]. Thus, this trial will generate evidence regarding the efficacy of TVS in pain perception in individuals with KOA. Finally, it should be noted that one limitation is that the therapists are not blinded to the patient’s treatment since they are in charge of placing the electrode in the ear, thus knowing in which group the patients are assigned. However, we do not believe that this will affect the intervention.

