### 2.6. Masking

Participants will be masked as to the study hypotheses, as they will not be informed about the group to which they were assigned. Likewise, the evaluators (who assess at the end of therapy and the follow-up at 1 and 3 months) will not know which group the participants were assigned. Participants and evaluators performing the various assessments will be asked about the group they believe participants were assigned. The masking of evaluators and patients will be maintained until the end of the investigation and data processing. See Figure 1.

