## Appendix A. Exercise Protocol

The exercise protocol is guided by general principles described below: 1.- The exercises should not increase the patient’s pain significantly. They can cause fatigue and a feeling of tiredness, but they should not increase the symptoms significantly; that is, if the patient feels the same pain when doing the exercise as when resting, he/she can do it without pain or with mild pain (VAS 30 mm. approximately). 2.- If a patient can exercise at one level without increasing their basal pain, he/she move to the next level. If the next level causes increased pain, the level should be decreased. 3.- Emphasis should be placed on the quality of the exercises’ execution and not on the repetitions or series. If a patient performs the exercise inappropriately, an attempt should be made to correct it. Stop the exercise if the patient is not able to continue with quality repetitions, that is, without compensation and in a coordinated and fluid manner. The patient should not perform apnea in isometric exercises. All exercises have the transversal objective of reducing pain.					
Objective	Level 1	Level 2	Level 3	Level 4	Level 5
Objective: To strengthen the quadriceps	Patient in a seated position. Isometric contraction of the quadriceps with the extended leg. Hold for 10 s and perform 10 repetitions. Alternating both legs.	Patient in supine position. Lifting of the extended leg. Hold for 10 s and perform 10 repetitions. Alternating both legs.	Patient in supine position. Lifting of the extended leg. Hold for 10 s and perform 10 repetitions with 2 kg at the distal part of the leg. Alternating both legs.	Patient in seated position. Knee extension with 2 kg at the distal part of the leg. 10 repetitions × 3 series. Alternating both legs.	Patient in seated position. Knee extension with 4 kg at the distal part of the leg. 10 repetitions × 3 series. Alternating both legs.

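### Unblinded physiotherapists judge exercise progression session by session, and the protocol's belief that their knowledge of the arm will not matter has no support

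*Protocol article*

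**What the plan says.** The Discussion (section 4) lists as a limitation that "the therapists are not blinded to the patient’s treatment since they are in charge of placing the electrode in the ear", and closes the matter with "we do not believe that this will affect the intervention".

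Under the exercise programme in section 3.5.2, "the physiotherapist in charge of administering the programme will assess session by session whether the difficulty of the various exercises should be adjusted". There are five levels and everyone starts at level 3. Appendix A gives the guiding rule: "If a patient can exercise at one level without increasing their basal pain, he/she move to the next level", with a step back down if the higher level increases pain. The programme's stated aims include reducing pain. The treating physiotherapists note attendance and progress in a record book.

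Sessions are supervised in person, "keeping a ratio of 1 physiotherapist per 3 participants at the most". The active clip goes on the left ear, "specifically in the auricular cymba concha"; the sham clip goes on the left earlobe. The device is worn for the whole session.

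On masking, section 2.6 says: "Participants will be masked as to the study hypotheses, as they will not be informed about the group to which they were assigned". It also has participants and evaluators guess the allocation. Section 3.5.1 keeps the assessors separate from the treating physiotherapists and blinded.

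**The concern.** Exercise is not a fixed background in this trial. It is tailored, it acts on the same symptom as the primary outcome, and the person tailoring it knows the arm. If a therapist, even unintentionally, pushes or encourages participants in one arm more than in the other, the arms differ in exercise received as well as in stimulation. The primary ANCOVA on 4-week VAS pain would attribute the sum of the two to stimulation. Blinded outcome assessment does not help, because the difference arises during treatment and is already in the participant's own pain rating.

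A second and weaker route runs through participant masking. Two visibly different clip positions on the same ear, worn throughout supervised sessions, could prompt participants to compare if the arms train side by side.

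**Working it through.** The plan attaches no figure to this point, so the main check sets its statements side by side.

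1. **Who knows the arm?** The treating physiotherapists (section 4).
2. **Who judges difficulty, and how often?** The physiotherapist administering the programme, with a review each session (section 3.5.2) over 12 sessions. A change is possible at each review, not automatic.
3. **How tightly is that judgement bound?** Appendix A ties moves to whether pain increases. It also speaks of pain not rising significantly, of mild pain being acceptable, and of the quality of execution. Each is read by the therapist, so the rule narrows discretion without removing it.
4. **Does the tailored component act on the primary outcome?** Yes. Section 3.5.2 gives pain reduction as an aim of the programme, and section 2.7 expects a considerable VAS reduction because of the exercise. The primary outcome is self-reported average pain over seven days (sections 3.2 and 3.6).
5. **Is the exercise received compared between arms?** In part. Session attendance is a secondary outcome (section 3.3), and section 3.6 analyses secondary outcomes with between-arm models. No comparison of level reached is described, although the record book holds progress.
6. **Does the same programme in both arms settle it?** No. It means the same set of exercises and levels, not the same progression.

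Steps 1 to 4 form a complete path from knowledge of the arm to the primary outcome. The sentence in section 4 denies the consequence without breaking any link.

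**Scale, as an assumption only.** Suppose unequal progression shifts the between-arm VAS contrast by b mm and stimulation has no effect. Take the SD of change from section 2.7 (21.5 mm) and 32 per arm (64/2).

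- Standard error = 21.5 × √(2/32) = 21.5 × 0.25 = 5.375 mm
- Chance of two-sided p < 0.05 = Φ(b/5.375 − 1.96) + Φ(−b/5.375 − 1.96)

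| b (mm) | Chance of a significant result |
|---|---|
| 0 | 5.0% |
| 2 | 6.6% |
| 4 | 11.5% |
| 6 | 20.0% |

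The document gives no value for b and no direction. The table shows only how sensitive the test is. If adjustment for baseline pain brings the residual SD below 21.5 mm, the same shift would raise these rates further.

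**The case against.** The strongest reply is that the design already contains sensible safeguards: one programme for both arms, six hours of training with written progression material, regular meetings to keep delivery uniform, a pain-based level rule, separate blinded assessors, and a group-guess question. This stands as far as it goes. These measures limit discretion or detect failed masking, but none blinds the therapist or shows that progression was equal.

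A second reply is that a by-arm table of exercise level is a detail that an article may leave to the full protocol or analysis plan. That is fair, and the point does not rest on the missing table. It rests on the article's stated belief, which its own description of the intervention does not bear out.

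Several stronger readings are tempting but not supported:

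- A reader might infer that the plan rules out any effect. It expresses a belief, and does so while naming a limitation.
- A reader might infer that difficulty is changed at every session. It is reviewed at every session.
- A reader might infer that participants see each other's clips and so learn their arm. The text does not say that ears are uncovered or that the arms exercise together; the ratio of three is a staffing cap. Noticing two sites would also not by itself show which one is active.
- A reader might infer that the double-blind label is false. The Abstract defines it as participants and outcome assessors, which is consistent with section 4.
- A reader might want the bias as a share of the target effect. No source supports any assumed shift, and the denominator is unclear: section 2.7 names 8.6 mm, whereas its f = 0.40 implies d = 2 × 0.40 = 0.80, or 0.80 × 21.5 = 17.2 mm.

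**Conclusion.** The concern holds in a limited form. Unblinded therapists exercise session-by-session judgement over a co-intervention that targets the primary outcome, and the statement that this will not affect the intervention is unsupported. Performance bias is therefore an open risk in the primary comparison that assessor blinding does not address. Its size and direction cannot be estimated from the document; the rates in the table rest on an assumed shift and serve only as illustration.

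The masking element is conditional. It matters only if participants from both arms exercise together with the clips in view, which the document neither states nor excludes. It justifies an inexpensive precaution, not a conclusion that masking fails.

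**What to change.** 1. **Prespecify a by-arm comparison of exercise level reached and progression over the sessions**, taken from the existing record book, and interpret the primary result in its light. Similar progression would be reassuring. A difference would need careful reading: because levels follow pain, a true stimulation effect could also move participants up faster. For that reason the comparison should be descriptive, and level should not enter the primary model as a covariate. Cost: one table from data already recorded.
2. **Cover the left ear identically in both arms once the clip is placed.** Cost: a simple cover, a little set-up time, and a check that the clip stays in position.
3. **Replace the sentence in section 4** with a plain statement of the performance-bias risk and of the safeguards above. Cost: none beyond the edit.

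Optionally, where both existing physiotherapists are present, one could place the clip and the other tailor the exercise. The document does not say that both attend every session, so this should not be a requirement. None of these changes alters the exercise rules or the stimulation settings.
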